
##### Patient satisfaction survey

Patient satisfaction will be assessed via an electronic survey that will evaluate the subject’s satisfaction with their participation in the study and identify particular areas for improvement with regard to the study protocol. Upon completion of the study, patients will be asked to provide both structured and open-ended responses to describe their experience. This data will be analyzed both quantitatively and qualitatively to guide future research.

##### Data collection

In addition to the data collected involving our primary and secondary outcomes, we will also collect information regarding patient demographics, clinical variables such as age and gender, surgical and anesthetic details, intensive care unit (ICU) and hospital length of stay, and patient mortality at 30 days and 6 months. Study data will be collected and managed using REDCap electronic data capture tools hosted at BIDMC. REDCap is a secure, web-based application designed to support data capture for research studies [25]. Designated members of the research team will be responsible for building and maintaining the electronic case report form, as well as monitoring data entry for completeness, timeliness, and accuracy.

##### Reporting of compliance and adverse events

A specialist within the research group will monitor protocol compliance, occurrence, and reporting of adverse events to the IRB.

#### Statistical analysis

##### Sample size calculation

A convenience sample of 45 patients will be chosen to assess the feasibility of perioperative neurocognitive training. A total of 20 enrolled and randomized subjects are needed per group to assess the rates of participation, adherence, and dropout associated with the study. To account for patients who may fail the initial MOCA screen or withdraw, we have added five patients to the desired enrollment sample size for a total planned enrollment of 45 patients.

##### Data analysis

Patients will be prospectively randomized using 1:1 block randomization. Analyses will be conducted using SAS version 9.4 (SAS Institute Inc., Cary, NC, USA) or later. Descriptive statistics of the data will be performed. Continuous data will be represented using mean (± standard deviation) or median (interquartile range) for variables not normally distributed and compared using parametric or non-parametric tests as appropriate. Categorical data will be presented as frequencies and proportions and compared using a chi-square or Fisher’s Exact test.

##### Analysis of the primary outcome

The primary outcome of the study is feasibility. Feasibility will be defined in terms of recruitment and adherence to protocol. Descriptive statistics of the data will be presented, including number of eligible patients and overall study consent rates. Reasons for declining participation will be documented and reported in aggregate. Adherence to the protocol will be assessed using automated data reports of user activity generated in collaboration with Lumosity. Per protocol, patients are expected to complete the intervention twice daily for at least 10 days preoperatively and 4 weeks postoperatively unless they are intubated or otherwise incapacitated due to critical illness. Adherence will be reported as the proportion of minutes completed over the total minutes required per protocol (calculated as 30 × [number of preoperative days + 28] minutes). Data will be reported for both the entire perioperative period, as well as individually for the preoperative and postoperative periods.

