### Study intervention: neurocognitive training

Patients will be randomized in a 1:1 allocation via a concealed block scheme to either intervention or control using the Research Electronic Data Capture (REDCap) randomization feature. Patients randomized to the intervention group will be asked to complete two 15-min neurocognitive training sessions per day, from the day of enrollment until 4 weeks after their day of surgery including the immediate postoperative in-hospital period. Our inclusion criteria were designed so that study participants with at least 10 days of lead-in time could then complete at least 5 h of training before surgery, with the understanding that there may be unequal durations of gameplay based on scheduling patterns among patients. The training instrument used in this study, Lumosity, was created by Lumos Labs Inc., San Francisco, CA, USA, as a web-based and mobile platform designed to improve performance in specific cognitive abilities through interactive gameplay. As part of a customized training program tailored towards cognitive abilities thought to be deficient in the postoperative period, patients in the intervention arm will train in each of the following categories per session: memory, attention, problem solving, flexibility, and processing speed. Participants in the intervention arm will be given a study iPad that is WiFi enabled and locked to the Lumosity program. Adherence to the study protocol will be quantified using automated gameplay data received from Lumos Labs. Unblinded study members will be responsible for providing technical support to participants as needed and for periodic checks on adherence between in-person assessments.

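### The adherence denominator counts days on which the protocol itself does not expect training, so the adherence part of the primary outcome is biased downward

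*Protocol article*

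**What the plan says.** All references are to the protocol article.

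- **Study intervention: neurocognitive training.** Patients in the training arm are asked to "complete two 15-min neurocognitive training sessions per day, from the day of enrollment until 4 weeks after their day of surgery", and this explicitly covers the early days in hospital: "including the immediate postoperative in-hospital period".
- **Analysis of the primary outcome, expectation.** Twice-daily training is expected before surgery and for four weeks after it, "unless they are intubated or otherwise incapacitated due to critical illness".
- **Analysis of the primary outcome, measure.** The next sentence reads "Adherence will be reported as the proportion of minutes completed over the total minutes required per protocol", and gives that total as "calculated as 30 × [number of preoperative days + 28] minutes".
- **Analysis of the primary outcome, reporting.** "Data will be reported for both the entire perioperative period, as well as individually for the preoperative and postoperative periods".

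Adherence is one of the two components of feasibility, the primary outcome. The other is recruitment, which has a stated criterion of 50% of eligible patients. No criterion is stated for adherence.

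**The concern.** The two adjacent sentences do not agree. If training is not expected on a given day, that day's 30 minutes are not required. The formula still counts them as required, because its 28 postoperative days are a constant. Nothing elsewhere in the article adjusts the denominator.

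The situation is foreseeable. All participants have cardiac surgery, the training schedule runs through the immediate postoperative stay, and the section on secondary outcomes plans for patients who are still intubated when they are assessed for delirium.

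What is at stake is how the adherence figure will be read when the larger trial is designed. Patients who could not train and patients who chose not to train call for different design responses. A figure labelled as a share of required minutes mixes the two and understates compliance with what the protocol actually asked. The effect falls mainly on the postoperative and overall figures. The preoperative figure is touched only if a patient is incapacitated before surgery.

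**Working it through.** **Inputs from the article**
- Daily requirement: 2 sessions × 15 min = 30 min (Study intervention).
- Minimum lead-in: 10 days (Inclusion criteria).
- Postoperative days in the formula: 28 (Analysis of the primary outcome).

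**Assumed input**
- k, the number of excused postoperative days per patient. The article gives no figure, so a range of 1 to 14 is shown.

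**Step 1. Reproduce the plan's own figure.** 30 min × 10 days = 300 min = 5 h, which matches the stated expectation of "at least 10 days of lead-in time could then complete at least 5 h of training before surgery". The denominator at 10 preoperative days is 30 × (10 + 28) = 1140 min, of which 30 × 28 = 840 min are postoperative.

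**Step 2. Highest attainable score under the stated formula.** For a patient with d preoperative days who completes every session except on k excused postoperative days:
- overall ceiling = (d + 28 − k) / (d + 28)
- postoperative ceiling = (28 − k) / 28

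| k | Overall, d = 10 | Overall, d = 30 | Postoperative |
|---|---|---|---|
| 1 | 37/38 = 97.4% | 57/58 = 98.3% | 27/28 = 96.4% |
| 3 | 35/38 = 92.1% | 55/58 = 94.8% | 25/28 = 89.3% |
| 7 | 31/38 = 81.6% | 51/58 = 87.9% | 21/28 = 75.0% |
| 14 | 24/38 = 63.2% | 44/58 = 75.9% | 14/28 = 50.0% |

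The loss per excused day is 1/28 = 3.6 points postoperatively. Overall it is 1/38 = 2.6 points at d = 10 and 1/58 = 1.7 points at d = 30.

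**Step 3. Group level, two assumed scenarios at d = 10.**
- Every patient has 1 excused day: the mean ceiling is 1 − 1/28 = 96.4% postoperative and 1 − 1/38 = 97.4% overall.
- 20% of patients have 7 excused days (0.2 × 7 = 1.4 days per patient on average): 1 − 1.4/28 = 95.0% postoperative and 1 − 1.4/38 = 96.3% overall.

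**Step 4. With excused days removed.** The denominator becomes 30 × (d + 28 − k). At d = 10 it is 1110, 1050, 930 and 720 min for k = 1, 3, 7 and 14, in place of 1140 each time. The postoperative part is 810, 750, 630 and 420 min, in place of 840. A patient who completes every expected session then scores 100%.

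**The case against.** The best defence is that a fixed denominator is a legitimate feasibility measure. It shows how much of the scheduled training this surgical population actually receives, and inability to train after surgery is part of that answer. This stands as a reason to keep the figure. It does not rescue the label: a scheduled total is not the total required per protocol when the preceding sentence waives some of it.

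It can also be said that the wording about required minutes already leaves out excused days. The explicit formula rules that reading out.

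Three further objections limit the weight of the point, and they stand.

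- **No decision hangs on it.** A reader might infer that the error could turn a feasible programme into an infeasible one. The article does not support that. The 50% criterion concerns recruitment only, and adherence is reported descriptively without a threshold.
- **Illness can be partly separated from unwillingness.** A reader might infer that a low postoperative figure could not be attributed at all. However, the article considers three training periods (preoperative, immediate postoperative and extended postoperative) and collects intensive care and hospital stay and mortality. These do not give a count of excused days, but they allow low adherence to be read against illness.
- **The large losses are individual cases.** Ceilings of 75% or 50% describe single patients with prolonged critical illness, whose frequency is unknown. Ten preoperative days is also the eligibility minimum, so it gives the largest overall effect.

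**Conclusion.** The point holds as an internal contradiction in the formula for one component of the primary outcome. It is not a detail left to another document, since the article states both the excusal and a formula that ignores it. Followed as written, the formula biases adherence to the protocol downward, by 3.6 points postoperatively per excused day in a fully compliant patient and by 2.6 points overall at 10 preoperative days.

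Across the arm, the likely size is modest: about 4 to 5 points of postoperative ceiling in the two scenarios shown. Those scenarios rest on assumed excused-day counts, and the true loss could be smaller or larger.

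Two further inferences should not be drawn. The article does not say that the postoperative period is where feasibility is most in doubt; it points to reliance on a patient-performed intervention and to recruiting patients with enough lead-in time. Nor does it say how days after a death or withdrawal are counted. The formula could be read as charging them, but an article commonly leaves such rules to the full protocol or analysis plan, so this is not counted as an error here.

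**What to change.** Reconcile the two sentences in Analysis of the primary outcome, without altering who is excused:

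1. Define protocol adherence as minutes completed / (30 × [preoperative days + 28 − documented excused days]). For the separate preoperative and postoperative figures, subtract the excused days that fall in that period.
2. Report a patient with no required postoperative days as not evaluable for that period. Otherwise the postoperative denominator would be 30 × (28 − 28) = 0.
3. Keep the existing fixed-denominator figure, relabelled as the proportion of scheduled dose delivered, and report the number of excused days per patient beside it.
4. Code excused days from the hospital record without sight of the gameplay data, under a rule written beforehand for what documentation counts and how part-days are handled.

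The cost is a change of analysis wording, chart abstraction and a second reported figure. Abstraction is needed because the daily blinded delirium assessments stop at discharge or day seven, so they cannot supply the count for all 28 days. The gameplay data are already automated, and no change to treatment or visits is needed.

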#### Study outcomes

##### Primary outcome: feasibility

To best evaluate the potential effect of a neurocognitive training program on the development of postoperative delirium and POCD, a large randomized controlled trial would need to be performed. However, before undertaking such a trial, it is imperative to show that implementation of a prehabilitative program is feasible. This is especially true given the heavy reliance on a patient-performed intervention and need for recruitment of interested subjects with sufficient lead-in time for the intervention to be effective. Furthermore, since this is the first time neurocognitive training will be implemented in this setting, there is no preliminary data regarding a potential effect size for an accurate power calculation to be performed. Therefore, the PEaPoD trial was designed to evaluate feasibility as a primary outcome. Feasibility will be assessed through both recruitment and adherence. Satisfactory recruitment will be defined as enrollment of 50% or more of eligible patients, which will reflect efficient screening and approach procedures and also sufficient interest within this patient population. Adherence will be quantified for analysis using automated gameplay data recorded during use. Consideration of three separate training periods (preoperative, immediate postoperative, and extended postoperative periods) will be taken into account in evaluating optimal adherence patterns for potential future study.

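### The adherence denominator counts days on which the protocol excuses patients from training, so a fully compliant patient can score below 100%; the reporting periods also need reconciling

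*Protocol article*

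**What the plan says.** All references are to the protocol article.

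- **Training asked for.** Study intervention: neurocognitive training asks for "two 15-min neurocognitive training sessions per day, from the day of enrollment until 4 weeks after their day of surgery including the immediate postoperative in-hospital" stay. That is 30 minutes a day, and the hospital stay after surgery counts as training time.
- **Exemption.** Analysis of the primary outcome repeats the twice-daily expectation before and after surgery, but qualifies it: "unless they are intubated or otherwise incapacitated due to critical illness".
- **Denominator.** The next sentence divides the minutes completed by the "total minutes required per protocol (calculated as 30 × [number of preoperative days + 28] minutes". Nothing is deducted for exempt days.
- **Periods.** Primary outcome: feasibility says: "Consideration of three separate training periods (preoperative, immediate postoperative, and extended postoperative periods) will be taken into account in evaluating optimal adherence patterns". Analysis of the primary outcome says: "Data will be reported for both the entire perioperative period, as well as individually for the preoperative and postoperative periods".
- **Threshold.** Recruitment has a success criterion (at least half of eligible patients enrolled). Adherence has none; it is reported as a proportion.

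**The concern.** Adherence is one of the two components of the primary outcome. The ratio is meant to compare what patients did with what they were asked to do. As written, the denominator carries the label of required minutes but includes minutes that the preceding sentence does not require.

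The error runs in one direction. It lowers the score of patients who were intubated or critically ill and leaves everyone else's score unchanged. Because the exemptions named would arise essentially after surgery, the preoperative figure is hardly touched while the postoperative and overall figures fall. The comparison of preoperative with postoperative adherence is then tilted against postoperative training. A low postoperative value could mean that patients would not train or that they could not, and those two explanations call for different designs of the next trial.

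The period split adds to this. The time just after surgery, when incapacity is most likely, is pooled with the later weeks in the reported postoperative figure, although the outcome section treats them as separate periods.

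**Working it through.** **Inputs from the documents**
- Daily dose: 2 × 15 = 30 minutes (Study intervention).
- Minimum lead-in: 10 days (Inclusion criteria; Study intervention).
- Postoperative days in the formula: 28 (Analysis of the primary outcome).
- Planned group size: 20 (Sample size calculation).

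**Assumptions**
- E, the number of exempt days per patient, is not given. I take 1 to 14 and place all of them after surgery.
- P, the number of preoperative days, is taken as 10 (the minimum) and, for contrast, 30.
- The patient trains exactly 30 minutes on every non-exempt day, which is full compliance.

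**The plan's own figure.** The article says that "study participants with at least 10 days of lead-in time could then complete at least 5 h of training before surgery". Check: 30 × 10 = 300 minutes = 5 hours. It reproduces, so 30 minutes per day is the right unit.

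**Formulas for a fully compliant patient**
- Overall score as written: 30 × (P + 28 − E) / [30 × (P + 28)] = (P + 28 − E) / (P + 28).
- Postoperative score as written: (28 − E) / 28.
- With exempt days removed from the denominator, both equal 100% for any E below 28.

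**Results at P = 10** (denominators 30 × 38 = 1140 minutes overall and 30 × 28 = 840 postoperatively)

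| Exempt days | Overall | Postoperative |
|---|---|---|
| 0 | 1140/1140 = 100% | 840/840 = 100% |
| 1 | 1110/1140 = 97.4% | 810/840 = 96.4% |
| 2 | 1080/1140 = 94.7% | 780/840 = 92.9% |
| 3 | 1050/1140 = 92.1% | 750/840 = 89.3% |
| 7 | 930/1140 = 81.6% | 630/840 = 75.0% |
| 14 | 720/1140 = 63.2% | 420/840 = 50.0% |

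**Sensitivity to lead-in.** At P = 30 the overall denominator is 30 × 58 = 1740 minutes, and 7 exempt days give 1530/1740 = 87.9% overall. The postoperative score stays at 75.0% because it does not depend on P. Each exempt day costs 1/38 = 2.6 points overall at P = 10, 1/58 = 1.7 points at P = 30, and 1/28 = 3.6 points postoperatively.

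**Effect on the arm mean, everyone fully compliant, P = 10**
- Every patient has 1 exempt day: 97.4% overall. With 2 days: 94.7%.
- A quarter of patients have 7 exempt days and the rest none: 1 − 0.25 × 7/38 = 95.4% overall, and 1 − 0.25 × 7/28 = 93.8% postoperatively.
- One patient of 20 has 14 exempt days: the postoperative mean falls by 50/20 = 2.5 points.

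**Periods side by side.** The outcome section names preoperative, immediate postoperative and extended postoperative. The analysis section lists the entire period, preoperative and postoperative. The second list contains no division of the 28 postoperative days.

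**The case against.** The strongest reply is that little hangs on the ratio. It is descriptive, no go/no-go rule or test uses it, and the sample is one of convenience. The numerator is automated gameplay data, so another denominator can be applied later wherever exempt days are documented. This is right, and it limits the consequences. It does not make the stated denominator agree with the stated exemption.

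A second reply is that a fixed denominator is a sensible feasibility measure: whether the full amount of training can be delivered in this population, illness included, is a fair question. That also stands, and it is a reason to keep the present ratio under a name that fits. It is not what the article's label says. A related caution is that being incapacitated is a judgement made after randomisation, so generous recording would raise the score. Showing both measures guards against that.

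Third, the losses above rest on assumed exempt-day counts, and 10 preoperative days is the value that makes the overall loss largest. This stands. Nothing in the article shows that 7 or 14 exempt days would be typical, and with 1 or 2 the loss is small. The article does foresee patients who are still intubated or cannot speak after surgery, since it provides the CAM-ICU for them, so zero exempt days for everyone is not its working assumption either.

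Two stronger readings are tempting, and the article does not support them:
- *Compliant patients are classed as non-adherent.* That would need a cutoff, and none is set. They receive a proportion below 100%.
- *Three-period results were promised, and the two-period report makes adherence patterns impossible to study.* The outcome section speaks of considering three periods, not of tabulating results for each, and the same gameplay data could still be divided in three. What remains is that the two sections do not match.

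**Conclusion.** The point holds as an inconsistency between an exemption and the formula that follows it. For patients with exempt days, the ratio understates adherence to what the protocol asked, in the postoperative and overall figures. For patients without such days it is correct.

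The size depends on exempt-day counts that the article does not give. For an individual it ranges from a few points (1 or 2 days) to 25 points postoperatively with 7 days and 50 points with 14. For the arm mean it is a few points in the scenarios worked above. These figures assume full compliance on every other day and exempt days falling only after surgery. The overall figures also depend on the length of the lead-in; the postoperative ones do not.

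The difference between two and three periods is a mismatch of wording to be reconciled, not a barrier to the analysis. Both matters deserve correction before analysis, because adherence is a component of the primary outcome and is meant to inform the next trial.

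**What to change.** 1. Define required minutes as 30 × (preoperative days + 28 − documented exempt days), an exempt day being one that meets the exemption already written in the article. This leaves the exemption itself as it is.
2. Keep the present ratio, with its fixed denominator, as a second measure labelled *dose delivered*.
3. Reconcile the two sections by reporting both measures for the preoperative, immediate postoperative and extended postoperative periods, as well as overall, and state where the immediate period ends.
4. Where a patient has no required days in a period, report adherence for that period as not applicable and give the number of such patients.

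**Cost.** One changed formula, one flag for exempt days and an additional column in the report. The gameplay data already planned should allow the split by period. The real burden is the flag: the daily delirium assessments stop at discharge or day seven, and the article describes no daily record after that, so later exempt days would have to be recorded prospectively or abstracted from clinical notes. The trial is under way and protocol amendments go to the IRB, so the change may need to be submitted there.
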